## Abstract

**Background::**

Rigorous evaluations of health system interventions to strengthen hypertension and cardiovascular disease (CVD) care remain scarce in sub-Saharan Africa. This study aims to evaluate the reach, effectiveness, adoption / acceptability, implementation fidelity, cost, and sustainability of the Ghana Heart Initiative (GHI), a multicomponent supply-side intervention to improve cardiovascular health in Ghana.

**Methods::**

This study adopts a mixed- and multi-methods design comparing the effects of the GHI in 42 intervention health facilities (i.e. primary, secondary and tertiary) in the Greater Accra Region versus 56 control health facilities in the Central and Western Regions. The evaluation design is guided by the RE-AIM framework underpinned by the WHO health systems building blocks framework, integrated by the Institute of Medicine’s six dimensions of health care quality: safe, effective, patient-centered, timely, effi cient, equitable. The assessment tools include: (i) a health facility survey, (ii) a healthcare provider survey assessing the knowledge, attitudes, and practices on hypertension and CVD management, (iii) a patient exit survey, (iv) an outpatient and in-patient medical record review and (v) qualitative interviews with patients and various health system stakeholders to understand the barriers and facilitators around the implementation of the GHI. In addition to primary data collection, the study also relies on secondary routine health system data, i.e., the District Health Information Management System to conduct an interrupted time series analysis using monthly counts for relevant hypertension and CVD specific indicators as outcomes. The primary outcome measures are performance of health service delivery indicators, input, process and outcome of care indicators (including screening of hypertension, newly diagnosed hypertension, prescription of guideline directed medical therapy, and satisfaction with service received and acceptability) between the intervention and control facilities. Lastly, an economic evaluation and budget impact analysis is planned to inform the nationwide scale-up of the GHI.

**Discussion::**

This study will generate policy-relevant data on the reach, effectiveness, implementation fidelity, adoption / acceptability, and sustainability of the GHI, and provide insights on the costs and budget-impacts to inform nation-wide scale-up to expand the GHI to other regions across Ghana and offer lessons to other low- and middle-income countries settings as well.

**RIDIE Registration Number::**

RIDIE-STUDY-ID-6375e5614fd49 (https://ridie.3ieimpact.org/index.php).

## Background

Cardiovascular diseases (CVD) are the leading cause of death globally, with a disproportionately higher burden (> 80% age-standardized CVD deaths) in low-and middle-income countries (LMICs) [1]. Arterial hypertension, also called high blood pressure (BP), is a leading modifiable risk factor associated with CVD death and disability [2]. While the average age-standardized BP is declining in most high-income countries, it is increasing in LMICs with 32%−50% of adults estimated to have high BP in sub-Saharan Africa (SSA) [3]. Multiple studies have shown that the key drivers of CVD in LMICs include insuffi cient physical activity, low fruit intake, high consumption of processed meat and sedentary lifestyles associated with rising urbanization as well as rising prevalence of hypertension, diabetes, obesity, and smoking [4] [5]. Although hypertension is a largely controllable condition, its actual rates of awareness, treatment, and control are disappointingly low in SSA. Ghana is a lower middle-income country in SSA with an estimated hypertension prevalence of 38%, and sub-optimal hypertension awareness (34%), treatment (32%) and control rate (2%−12%) [6] [7] [8]. A 5-year review of autopsy cases (January, 2006 to December, 2010) at Korle Bu Teaching Hospital, the largest and leading supra-tertiary level national referral and teaching hospital in Accra has attributed 22.2% of all deaths to CVD [9]. In addition to the disease burden, CVD threatens to impose a significant economic burden in Ghana, with more than 40–50% of households paying out-of-pocket for health services and medications [10]. Although there is a National Health Insurance Scheme, it has traditionally covered outpatient visits to improve access for many people, with recent expansion to inpatient care coverage although some services at tertiary level hospitals are not included in the benefit package. Additionally, there are delays in reimbursement of claims to facilities that affect the health system’s ability to provide timely management of hypertension and CVD [11].

Evidence from meta-analysis of randomized trials have shown that lowering BP reduces the risk of future stroke by 35%−40% and myocardial infarction by 20%−25% [12]. However, uptake of proven CVD therapies is sub-optimal globally such that there is a 55%-point gap in the effi cacy of CVD treatment shown in clinical trials versus real world effectiveness [13] [14]. Several health system factors in the LMIC context ostensibly influence the poor uptake of CVD prevention therapies and access to care, including the lack of standardized CVD treatment guidelines, acute shortage and inequitable distribution of trained health care workers, insuffi cient health system infrastructure and distribution of health care facilities, profound lack of laboratory facilities, supplies, and equipment including sphygmomanometer, medication stock-outs and high treatment costs [15]. The management and prognosis of high-risk patients depend on well-staffed emergency rooms and critical care units, which are poorly designed and developed in SSA, including Ghana. Further, recent reports from Ghana indicate large gaps in provider training, patient education, and medication availability to manage hypertension [16]. Given the rising CVD burden and relatively lower rates of hypertension control in Ghana, well-designed innovative models of healthcare delivery are urgently needed for early detection, treatment and follow-up of hypertension and CVD [17].

The Ghana Heart Initiative (GHI) initiated in September 2018, and offi cially launched on 9th January 2019, introduced an innovative health system intervention to strengthen early detection, and management of hypertension and CVD across health facilities in the Greater Accra Region (GAR). The initiative was implemented as a collaborative effort by the Deutsche Gesellschaft für Internationale Zusammenarbeit (GIZ) GmbH, Ministry of Health (MoH) and the Ghana Health Services (GHS). The GHI (“the intervention”) enables frontline healthcare workers to better address the needs of patients and communities and support advocacy and policy that promotes effective care for CVD. The intervention does not target the single patient but changes the quality of care given to the single patient, by changing the way the health system addresses the management of risk factors (such as hypertension) and CVD. The overarching goal of this study is to conduct a rigorous evaluation of the GHI, a supply-side intervention implemented in 42 diverse health facilities (primary to tertiary care level) for the prevention and management of hypertension and CVD in the GAR, adopting a mixed-methods implementation science approach.

## General objectives and research questions

Adopting an implementation science approach, our study aims to assess the reach, the effectiveness, the fidelity, the implementation process, the maintenance, and will provide scientific evidence for scaling-up the intervention nationwide. The study is envisioned to provide important insight into barriers and facilitators of scaling up a supply-side quality improvement CVD programme in Ghana. The specific research questions are:

Has the Ghana Heart Initiative reached the target population?Has the Ghana Heart Initiative produced the desired changes on quality of hypertension / CVD service delivery i.e., *safety, effectiveness, timeliness, equitable, and patient-centered care* and health outcomes?Has the Ghana Heart Initiative obtained support from key stakeholders?Has the Ghana Heart Initiative been delivered as planned (fidelity)?Are the implementation approach and health system changes produced by the Ghana Heart Initiative sustainable?

## Methods

### Study Setting

Ghana is a lower-middle-income country with an average annual per-capita gross domestic product of US$2,445.3 [18]. The mortality from coronary heart disease in 2020 was 119.93 per 100.000 population, and the probability of dying from any of CVD, cancer, diabetes and chronic respiratory disease is 20.8% [19]. The health system in Ghana is decentralized, pluralistic, and operates on an integrated three-tier (national, regional, and district) scheme and incorporates a community-level health delivery system to support community-based primary healthcare [20]. Most healthcare is provided by the government and is largely administered by the service delivery agencies under the MoH such as the Ghana Health Service (GHS), teaching hospitals, and the private providers (self-financing, faith-based, and non-governmental organisations). Ghana reformed its National Health Insurance Scheme in 2003 with 40% of the population being enrolled and ~ 60% enrolled people are exempted from premium payments [21]. Ghana is one of the first African nations to enact legislation and earmark financing for universal health coverage; a significant move towards health system strengthening and improved financial protection [21].

Accra is the capital city of Ghana and is located in GAR, which is one of the 16 administrative regions, and has the highest population density. The GAR has 26 districts, including the Accra Metropolitan Assembly, and had a total population of 5.4 million in 2021. The pilot phase of the GHI was implemented in 42 health facilities located in five districts (Accra Metro, Tema Municipal, Ga East, Ga West, Dangme West and Dangme East). A health facility is an infrastructure built and licensed by the Health Facilities Regulatory Authority to take care of the healthcare needs of the citizens of Ghana.

The comprehensive evaluation is being conducted in those 42 health facilities implementing GHI with matched control health facilities. Matching of intervention and control facilities was done based on pre-determined variables such as the level of care (primary, secondary, or tertiary), volume of outpatient visits, bed capacity and availability of human resources (number of physicians, nurses, and other allied healthcare professionals). The data on the facility level characteristics was obtained from the GHS and the Christian Health Association of Ghana (CHAG) Secretariat (the largest faith-based health service provider in Ghana) and we considered a large pool of potential ‘control’ health facilities from the Central Region and Western Region (Fig. 1). The advantage of using a quasi-experimental design with matched control facilities ensures that all the exposure variables stay the same across the intervention and control facilities except for the intervention arm, i.e., GHI-related activities.

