### Quantitative study component

For the assessment of the health service delivery performance between the intervention and control facilities, we are utilising mixed methods and multiple survey tools. Individual methods are chosen strategically based on the research question as well as considering feasibility and practicality [27]. Data is being collected at the facility-, provider- and patient-level using multiple surveys:

**Health facility assessment survey**: to determine the existing infrastructure, human resources, availability of services for hypertension and CVD, availability of laboratory tests and diagnostics, medicines for hypertension and CVD treatment and health service delivery indicators related to hypertension and CVD.**Provider survey**: to examine the knowledge, attitudes, and practices (KAP) regarding CVD and hypertension management as well as the acceptability of the GHI from provider’s perspective in intervention facilities only.**Patient exit survey**: patients asked post-consultation about the provision of care in the consultation to assess patient experiences and satisfaction with the hypertension or CVD related care received at the intervention and control facilities.**Medical record review**: before and after the implementation of the GHI to assess differences in hypertension and CVD care practices between intervention and control facilities.

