For the provider KAP survey and exit survey, the field data collection team(s) visit a health facility and capture a random sample of healthcare providers and patients available on the day of the visit. This method relies on random sampling and the effi ciency of the field team. In essence this means maximizing the number of potential respondents to be interviewed on the day of the visit i.e. all eligible patients exiting the facility are interviewed, all eligible healthcare providers present and available at the facility are interviewed [28] [29]. The field work is carefully timed so that it coincides with the day of a hypertension / CVD clinic. Prespecified **eligibility criteria** is applied for health facilities and study participants (providers and patients) for the quantitative evaluation. The health facility assessment survey is carried out in all GHI intervention facilities, and matched control health facilities to specific characteristics (example, level of care, volume of patients attending the clinic, bed size, human resources available, etc.). The provider survey is recruiting providers (doctors, nurses, physician assistants, pharmacists) aged 18 years and above, both males and females; presently working in the facility at least from the last 3 months. Further, a licensed provider is defined as a physician or a nurse, pharmacist or physician assistant who is directly involved in providing CVD related services (counseling, health education, or consultation services or pharmacological therapy). The provider survey excludes those healthcare workers who have a managerial position and do not provide any patient care. Also, a physician, nurse or pharmacist who has worked in the facility for less than 3 months is excluded from the provider survey. The patient exit survey is carried out among those aged 18 years, both males and females, and having physician diagnosis of hypertension or other CVD conditions. The exclusion criteria include patients having diseases associated with frequent hospitalization (advanced cancer, end stage renal disease) bedridden or debilitating conditions. The MRR is performed for the patient folders for those aged 18 years and above, both males and females, and having physician diagnosis of hypertension or CVD conditions-Medical records from 2018 to 2022 are being reviewed. The medical records of pregnant women and those patients having diseases associated with frequent hospitalization (advanced cancer, end stage renal disease); bedridden or debilitating conditions are excluded for the MRR.

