The medical records of outpatient and inpatient folders at two cross-sectional timepoints before and after GHI implementation are being reviewed to assess between group differences in hypertension and CVD care delivery. Eligibility of medical records are pre-specified based on confirmed diagnosis of hypertension or CVD, and complete medical records with at least data available on patient demographics (age, sex), medical history (confirmed case of hypertension or CVD), laboratory results (any test prescribed, or test reports reviewed), and medical treatment or prescription.

Lastly, DHIMS2 data routinely collected by the MoH in Ghana to monitor service provision consisting of monthly facility-specific counts for a wide range of services, including CVD will be analyzed to assess the differences in care delivery between the intervention and control health facilities over the time period. In line with prior work, to translate monthly counts into indicators that adequately capture service coverage, we construct outcome variables that account for the underlying target population living in the catchment area of a given facility [32]. More specifically, we apply interrupted time series analysis to DHIMS2 data to assess impact on the following CVD indicators: prevalence of hypertension, coronary heart disease, stroke, heart failure and related mortality.

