### Study outcomes

The primary outcome measures being assessed between the intervention and control facilities are: i) proportion of screened individuals for hypertension, ii) newly diagnosed patients with hypertension or CVD, iii) prescription of guideline directed medical therapy for hypertension and CVD, iv) BP control defined as < 140/90 mmHg, v) provider knowledge and practice related to hypertension and CVD and vi) patient centered care and satisfaction. The study also assesses several secondary outcome measures including difference in total waiting time for physician consultation and physician acceptability of the GHI.

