### Evaluation Design Strengths and Weaknesses

The mixed-methods triangulation study is the first of its kind for LMICs and in sub-Saharan Africa, testing a comprehensive and multifaceted health system intervention addressing hypertension and CVD management. The evaluation is rigorously designed, factoring in multiple data sources, minimizing biases using matched control health facilities, data triangulation using quantitative survey and qualitative interview data, and economic evaluation. The ToC was developed in a participatory manner in collaboration with GHI programme implementers helping the evaluators to understand where the intervention tried to produce a change and led to a commonly defined TOC and definition of indicators. Our focus is centered more on a theory-driven evaluation and the fact that we will work “closer to reality” but far from a real experiment or quasi-experiment. To avoid contamination between the intervention and control facilities, the data collection for control group facilities and participants will be accomplished by a separate team of trained field enumerators. However, in a real-world setting we cannot avoid spillover of intervention components to other regions since the national guidelines for the management of CVD were signed by the Minister of Health in 2021 and offi cially launched in August 2022 by the MoH and is available in the public domain and can be accessed via the AkomaCare App (https://akomacare.org/download) [47]. The data collection timepoints for the MRR before and after GHI implementation has been prespecified in both the intervention and control health facilities to avoid any seasonal variations in the hypertension and CVD care outcomes. Furthermore, we customized the survey questionnaires developed with an open-source platform called Survey Solutions (https://mysurvey.solutions/en/) developed by the World Bank. Data is entered on Android-based tablets using the Survey Solutions Interviewer App, stored locally on the tablets, and synchronized regularly to HIGH’s virtual server, enabling real time tracking and remote data monitoring. The Survey Solutions Designer allows the inclusion of instructions visible in blue for each question as the interviewer progresses through the survey. This digital data collection approach along with its technical features improves data quality and reduces data entry errors or missing values.

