The study has several limitations. As health facilities are not randomly assigned to the intervention and control arms, it is possible that the arms will be imbalanced about important patient characteristics (age, disease patterns, severity), provider characteristics (education, professional training or practicing experience), facility characteristics (primary, secondary and tertiary) and ownership (public, quasi-government and faith-based). These would be addressed in analyses adjusted for any important patient or provider-level characteristics. Mixed methods (quantitative and qualitative assessments) data evaluation will complement the overall data triangulation and analytical approach. Another potential limitation of the evaluation process may be recall bias when obtaining interview data after the pilot implementation phase of the intervention, as adherence may vary.

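### Matching cannot make the Greater Accra and control facilities alike in everything but GHI, and knowledge scores and satisfaction ratings have no described baseline to support causal attribution

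*Protocol article*

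**What the plan says.** Study Setting describes matching on variables such as level of care, outpatient volume, bed capacity and staffing. It then says that the quasi-experimental design with matched controls "ensures that all the exposure variables stay the same across the intervention and control facilities except for the intervention arm". The Abstract places all 42 intervention facilities in Greater Accra and all 56 control facilities in Central and Western.

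Study design also calls the study quasi-experimental. Evaluation Design Strengths and Weaknesses says that the work is "far from a real experiment or quasi-experiment" and, because facilities were not randomised, that "it is possible that the arms will be imbalanced about important patient characteristics". It extends that concession to provider and facility characteristics, including level of care and ownership.

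Study outcomes lists among six primary outcomes "v) provider knowledge and practice related to hypertension and CVD and vi) patient centered care and satisfaction", to be assessed between intervention and control facilities. Under Quantitative study component, field teams "capture a random sample of healthcare providers and patients available on the day of the visit", and in the exit survey "patients asked post-consultation about the provision of care". Collection before and after GHI is attached to the medical record review, used "before and after the implementation of the GHI to assess differences in hypertension and CVD care practices between intervention and control facilities". The data collection section repeats this: "The medical records of outpatient and inpatient folders at two cross-sectional timepoints before and after GHI implementation are being reviewed".

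Conceptual framework links causal attribution to difference-in-differences (DID), hoped for on some indicators, and to interrupted time series analysis (ITSA) if routine data are available.

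**The concern.** The second research question asks whether GHI produced the desired changes in quality of care, and it names patient-centred care. An answer needs either a comparison free of prior differences or a way to remove them. The sentence in Study Setting tells the reader that the first condition is met. It is not, and the same article says so elsewhere.

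For outcomes with pre and post data the overstatement does limited harm, because a before-and-after contrast can remove a stable regional difference. For knowledge scores and satisfaction ratings no such contrast is described. Someone relying on the Study Setting sentence could read a long-standing difference between the capital region and two other regions as the result of GHI. The findings are meant to inform nationwide scale-up.

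**Working it through.** The protocol states no figure that decides this point, so the check is mainly a comparison of its sections.

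**1. What matching can balance.** The listed variables are level of care, outpatient volume, beds and staffing. Earlier provider knowledge, earlier patient satisfaction and region are not among them. The limitations text allows imbalance even on level of care, which is a matching variable. So 'ensures' is not supported even for the matched variables.

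**2. Arm and region.** Every intervention facility is in one region and every control is in the two others. No facility with GHI lies in a control region, and no control lies in Greater Accra. A region term in a regression, or region in a propensity score, would therefore predict arm perfectly. Region and GHI cannot be separated within a single time point.

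**3. Is there a survey baseline?**
- Quantitative study component and the data collection section attach before and after to the record review.
- In Study components the before-and-after wording closes a list of tools, directly after the record review. The two sections above support reading it as belonging to that item.
- The first GHI phase ran 2018–2020 (Study intervention). The evaluation was designed between April and July 2022 (Study design).
- The limitations text places interview data after the pilot phase.

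No pre-GHI round of the provider or exit survey is described, and a visit-day interview cannot be held retrospectively.

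**4. What each contrast estimates.** Let τ be the GHI effect, and let g₀ and g₁ be the regional difference that would exist without GHI, before and after, once measured covariates are adjusted for.
- Post-only contrast: τ + g₁.
- DID: (τ + g₁) − g₀ = τ + (g₁ − g₀), which equals τ if the regional difference is stable.

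For knowledge scores and satisfaction ratings g₀ is not observed, so g₁ stays in the estimate.

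**5. What adjustment removes.** Statistical analysis plans random-effects models and a propensity score, and the limitations text plans adjustment for patient and provider characteristics. The knowledge model adjusts for age, sex, facility type and worker type. These reduce g₁ as far as the covariates explain it. None is a baseline value of the outcome.

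**6. Illustration only.** The protocol gives no size for g₁, so the values here are assumptions. Take the exit survey: 1,200 × (1 − 0.20) = 960 evaluable, assumed to split 480 per arm. Assume a binary rating with a 60% control rate, τ = 0, a residual gap d, and a two-sided 0.05 two-proportion test without clustering. With se₀ = √[2p̄(1−p̄)/480] and se₁ = √{[p(1−p)+q(1−q)]/480}, where q = p + d and p̄ is their mean, the chance of a significant result in the positive direction is 1 − Φ[(1.96·se₀ − d)/se₁]. The opposite tail is added.

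For d = 0.05: se₀ = 0.03125 and se₁ = 0.03121, so (0.06125 − 0.05)/0.03121 = 0.36 and the probability is about 0.36.

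| Residual gap (points) | 0 | 2 | 5 | 7 | 10 |
|---|---|---|---|---|---|
| P(significant), τ = 0 | 5% | 10% | 36% | 62% | 90% |

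At a 5-point gap the figure is 34% with a 50% control rate and 41% with a 70% rate. A random-effects analysis that allows for clustering would reject less often, but the bias in the point estimate would be the same.

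**The case against.** The strongest reply is that the protocol is already more careful than one sentence suggests. Conceptual framework says that only some indicators may support an impact estimate, and it ties causality to DID or ITSA. The outcome and analysis sections describe the survey results as comparisons between arms, not as effects. Non-random assignment and possible imbalance are disclosed, and several adjustments are planned. The evaluation was designed after the first phase, so a survey baseline can no longer be collected. The research question names patient-centred care but not provider knowledge.

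Most of this stands, and it limits the point. A reader might infer that the plan explicitly claims causality for knowledge and satisfaction. It does not. The problem is a general assurance in Study Setting that would license such a claim, together with a research question about what GHI produced.

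A reader might also infer that the record review is the only source with a time dimension. It is not, since the routine DHIMS2 data are monthly. Nor can all of the fifth and sixth outcomes be called post-only. Provider practice may draw on the before-and-after record review, and Table 1 also links patient-centred care to follow-up indicators from the health facility survey.

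The reply does not rescue the sentence itself. Disclosure in one section does not correct a contrary assurance in another, and adjustment for measured covariates does not stand in for a missing baseline when arm and region coincide.

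**Conclusion.** The sentence in Study Setting claims a property that the design lacks, and it conflicts with the limitations text. The quasi-experimental label in Study Setting and Study design conflicts with Evaluation Design Strengths and Weaknesses. For provider knowledge scores and patient satisfaction and experience ratings, the plan supports an adjusted post-implementation difference between regions, not a change produced by GHI.

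The size of the bias is unknown. It is tempting to say that the whole prior regional difference would appear as effect, but matching and adjustment may remove part of it. Only the remainder counts, and the documents give no value for it. The probabilities above rest on assumed gaps, an assumed control rate, equal arms and no clustering. They do not represent the planned analysis.

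The conclusion rests on reading before and after as applying to the record review, which the more specific sections support. If a pre-GHI survey round exists, the part about these two measures falls away and the wording conflict remains.

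**What to change.** 1. In Study Setting, replace the 'ensures' sentence with a statement that matching aims to reduce differences on the listed facility variables only.
2. Reconcile the design label in Study Setting and Study design with Evaluation Design Strengths and Weaknesses, so that the article describes the design in one way.
3. State, in line with Conceptual framework, that causal language is reserved for outcomes with pre and post data, analysed by DID (record review) or controlled ITSA (DHIMS2) where these can be carried out.
4. Report knowledge scores and satisfaction and experience ratings as adjusted post-implementation differences between regions. Say for each part of the fifth and sixth outcomes which source it comes from and whether that source has pre-GHI data.

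Using exit-survey items that GHI did not target as negative controls may seem attractive. The content of the 27 rated aspects is not shown, so the documents do not establish that such items exist, and the approach would not help with provider knowledge. It is not part of this recommendation.

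No new data are needed. The cost is a weaker claim for the survey-measured parts of two of the six primary outcomes.
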